### Sample Size

To detect a difference of 15 minutes (assuming within-person SD of 35 minutes) in TST [60], with 90% power at a .05 α level, a sample size of 60 participants would be required. We will recruit 72 children, allowing for 20% nonadherence, dropout, or incomplete data.

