#### Baseline (Week 1)

At the baseline appointment, researchers will explain the study protocol to potential participants and their caregivers (mainly parents), with opportunities for questions throughout. If the child and their caregiver indicate that they would like to be involved, they will be given a paper version of the assent (child) and consent (caregiver) form to sign. Once consent and assent are signed, caregivers will complete an online demographics questionnaire assessing the child’s date of birth, household address, and ethnicity. Weight (using Tanita electronic scales HD351) and height (using Wedderburn Portable Height Rod, WS-HRP) will be measured by trained researchers using standard procedures [62].

Participants will be given an accelerometer (AX3 [Axivity]) to wear on their nondominant wrist for 7 nights, 24 hours per day, to measure usual sleep (more details are discussed in the *Intervention Adherence* section). To determine usual bedtime practices in terms of screen time, physical activity, and food consumption, participants will be asked to wear a wearable video camera from 90 minutes before bedtime until bedtime on their 3 “intervention” nights (more details are discussed in the *Intervention Adherence* section). A second stationary camera in the child’s bedroom will face the bed and allow researchers to measure in-bed electronic use or eating, and to measure when the participants attempt sleep (shut-eye time; more details are discussed in the *Sleep* section). Participants will be asked not to change their behavior during the baseline week. Information from the cameras will also be used to give researchers insight into how the participants might be able to adapt their nighttime behavior to complete the intervention weeks. Researchers will talk to participants (and families) at the baseline visit about their usual eating, physical activity, and screen time habits to help develop personalized suggestions for completing the intervention weeks.

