### Randomization

#### Overview

Once the baseline appointment is completed, participants will be randomized using the REDCap (Research Electronic Data Capture; Vanderbilt University) randomization module [63] to one of 4 intervention group orders using a computer-generated sequence, stratified by age (from 10 to less than 13 years or from 13 to 15 years), with random block sizes of 4 or 8. The 4 group orders are from a Williams Latin square balanced for first-order carryover effects. Usual bedtimes will be discussed with families, based on camera footage from baseline. While bedtime for each night of intervention (ie, nights 5-7 of each intervention week) can be different, each day of the week must be consistent between all 4 intervention weeks.

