### Statistical Analyses

Siblings in the same family may wish to participate, and they would be convenient participants, given their familiarity with the intensive intervention protocols. However, siblings represent family clustering that must be statistically accounted for. We examined the intraclass correlation coefficient (ICC) for families in our recent observational repeated-measures study of screen use and sleep in teens [73], which was low (ICC=0.005). Using this ICC and an average family cluster size of 2, the design effect is 1.005 [74], which has a negligible effect on the required sample size (60*1.005=60.3). Therefore, siblings may be recruited but will be assessed at different times throughout the year, will be individually randomized, and will contribute to no more than half the sample (ie, n=36 participants must not have siblings in the study).

Primary statistical analyses will be undertaken using data from adherent days; secondary analyses will use all data. Mixed effects regression models with a random effect for participants nested within a family cluster will be used to estimate mean differences, 95% CI, and *P* values for conditions 2, 3, and 4 compared with condition 1. Residuals will be plotted and visually assessed for homoskedasticity and normality. Adjustments for within-person confounding (eg, lunar phases) will be undertaken as sensitivity analyses. Results will be reported in line with the CONSORT (Consolidated Standards of Reporting Trials) statement extension to crossover trials. Descriptive analyses will also be undertaken to explore participants’ experiences with the interventions as well as their adherence. Relationships between sleep and quality of life measures will be assessed using repeated measures mixed effects analyses.

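### With only adherent nights analysed, the random participant effect lets differences between children into the TST contrasts; these should be estimated within child

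*Protocol article*

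**What the plan says.** Two written choices in the article's Statistical Analyses section combine here. On the data: "Primary statistical analyses will be undertaken using data from adherent days"; the analysis of all data is secondary. On the estimator: "Mixed effects regression models with a random effect for participants nested within a family cluster will be used to estimate mean differences", with conditions 2, 3 and 4 each compared with condition 1.

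The Intervention Adherence section defines the nights that survive. Condition A allows under 5 minutes of screens in the hour before bed, and condition B requires at least 30. All conditions also limit the other behaviors. Study Design gives 3 nights per child per condition, and Randomization uses a Williams Latin square.

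The trial also measures usual sleep in week 1: children are given an accelerometer "to wear on their nondominant wrist for 7 nights, 24 hours per day, to measure usual sleep". The only adjustment that the article names is for within-person factors such as lunar phase, as a sensitivity analysis. It gives no list of fixed effects.

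**The concern.** A crossover is chosen so that each child is his or her own control. With all 12 intervention nights present, every child has the same mix of conditions, and a random participant effect gives purely within-child contrasts.

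The primary data set is not of that kind. After nonadherent nights are removed, one child may keep three B nights and one A night, another the reverse, and some may have no night in a condition. The random intercept then treats part of the difference between those two children as information about B versus A.

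The opposed rules for A and B give a plausible route to bias. A habitual evening screen user can easily fail A and pass B. If such children usually sleep less, their shorter usual sleep is partly credited to screens, even when adherence depends only on the child and not on the particular night. The Introduction criticizes earlier evidence for being cross-sectional, and this estimator lets some cross-sectional comparison back into the primary result.

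**Working it through.** **1. The plan's own figure.** Target 15 minutes, SD 35 minutes, "with 90% power at a .05 α level" (two-sided assumed), from Sample Size. Paired comparison, with 35 taken as the SD of the within-child difference: ((1.960 + 1.282) × 35/15)² = 57.2, so 58. With the noncentral t distribution it is 60 (power 0.904), which matches "a sample size of 60 participants would be required". The size of the trial is therefore not at issue; 15 minutes is the yardstick for the bias.

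**2. How between-child information enters.** Let σ_b be the between-child SD, σ_w the nightly SD and n the child's analysed nights. A random intercept removes the fraction nσ_b²/(σ_w² + nσ_b²) of the child's own level and leaves σ_w²/(σ_w² + nσ_b²). A participant fixed effect leaves none. The article gives no between-child SD and does not say whether its 35 minutes is nightly, so both SDs are assumptions.

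- σ_b = 40, σ_w = 35: 1225/20425 = 0.060 at n = 12; 1225/10825 = 0.113 at n = 6.
- σ_b = 45, σ_w = 50: 2500/26800 = 0.093 at n = 12; 2500/14650 = 0.171 at n = 6.

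With complete data the fraction left is harmless, because all children have the same mix of conditions. With unequal nights it carries their usual sleep into the contrast.

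**3. Simulation with no true effect.** 72 children, 4 conditions, 3 nights each; 1,500 to 2,500 trials per scenario; generalized least squares with known variances. The chance that a night is adherent depends only on the child's usual TST, through a logit slope per SD. Bias of B minus A in minutes; ranges cover the two SD pairs in step 2 and repeat runs:

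| Adherence and slopes | Stated model | Plus baseline TST | Participant fixed |
|---|---|---|---|
| 70%; +0.8 in A, -0.8 in B | -1.7 to -3.0 | -0.9 to -1.6 | about 0 |
| 50% in A, 70% in B; same slopes | -2.4 to -4.8 | -1.2 to -2.5 | under 0.3 in size |
| 70%; +0.4 in A, -0.4 in B | -0.8 to -1.6 | -0.4 to -0.8 | within 0.3 |
| 70%; +0.8 in A only | -0.9 to -1.6 | not run | not run |
| 80%; +0.8 in A, -0.8 in B | -1.2 to -1.8 | not run | not run |
| 80%; +0.8 in A only | -0.5 to -1.0 | not run | not run |
| Same slope in every condition | about 0 | not run | not run |

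The SD of the estimate was 3.8 to 6.9 minutes. A smaller check with variances estimated by REML (150 trials, SDs 45 and 50, about 70% adherence, first-row slopes) gave -3.2, -1.7 and -0.2. About 12% of children then lacked any A or any B night.

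**4. A wider range of adherence.** Nightly SD 35, between-child SD 30 to 60, slope 1 in A only, adherence stated for a child of average usual TST, baseline assumed to explain half the between-child variance:

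| Adherence | Stated model | Plus baseline TST | SD of estimate |
|---|---|---|---|
| 80% | -0.5 to -1.0 | -0.4 to -0.9 | 3.8 to 3.9 |
| 60% | -1.1 to -1.9 | -1.0 to -1.6 | 4.6 to 4.7 |
| 40% | -2.4 to -3.7 | -2.2 to -2.9 | 5.6 to 5.8 |
| 20% | -6.2 to -7.9 | -5.1 to -5.6 | 7.9 to 9.3 |

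Participant fixed effects stayed within 0.3 minutes of zero throughout. When nights were lost at random, or with the same slope in all conditions, the stated model's bias was within simulation error (0.25 or less).

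**5. Price of fixed effects.** The SD of the estimate rose by about 1% or less at 50% adherence and above in step 3. In step 4 it rose by about 2% at 40% (5.78/5.65 = 1.023) and 8% at 20% (8.71/8.06 = 1.081).

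**The case against.** A random participant effect is an ordinary crossover model, and unequal nights alone do not bias it. The slopes that produce the larger figures are assumed, they run in opposite directions for A and B, and nothing in the article shows them. The only loss allowance stated is "We will recruit 72 children, allowing for 20% nonadherence, dropout, or incomplete data". It is not expressly a rate per night, but it lends no support to the 50% scenario. At 80% adherence the bias is about 0.5 to 1.8 minutes, under half a standard error. The upper figures also need a nightly SD of 50, while the article's only SD is 35. Home visits, tailored suggestions and text reminders should limit nonadherence. The secondary analysis of all data largely restores the balance, since nonadherent nights are not dropped.

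All of this stands as a limit on size. It does not remove the point, because the analysis labelled primary is the one exposed, and the article names no within-child alternative for it.

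A reader might go further and infer that the model ignores baseline TST and the age stratum used in randomization. The article does not support that. It describes the random effects, the contrasts and one class of sensitivity adjustment, and excludes no covariate. A covariate list is commonly left to the analysis plan. Nor would these covariates be the cure: baseline TST removed about half the bias in step 3 and 6% to 31% in step 4. Both are constant within a child, so they drop out once participant is a fixed effect.

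**Conclusion.** The point holds as a limited weakness in the estimator. Adherent nights plus a random participant effect give up part of the within-child protection that the crossover was designed to provide.

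Whether this produces bias depends on adherence relating to usual TST differently by condition, which is plausible from the A and B rules but not shown. Under the opposed slopes, the B minus A bias is about -2 to -3 minutes at 70% adherence (13% to 20% of the 15-minute target) and -2.4 to -4.8 at 50% in A and 70% in B. It is about -0.5 to -1 minute at 80% with a slope in A only, and zero if adherence is unrelated to usual TST. In the first case and its half-slope variant, that is roughly 0.2 to 0.6 of a standard error. It can move confidence limits and P values, which matters because the Discussion expects limited effects.

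A reader might infer that the primary analysis could produce a spurious effect near 15 minutes. No scenario run here supports that; the bias exceeds 5 minutes only at the assumed 20% adherence.

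The conclusion rests on the assumed SDs, adherence levels and slopes. The mechanism, and its removal by within-child estimation, do not depend on their exact values.

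**What to change.** In Statistical Analyses, state that the adherent-night TST contrasts are estimated within child, in one of two ways:

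- fit participant as a fixed effect, in which case family is absorbed; or
- keep the random participant effect and add each child's share of analysed nights in each condition (three of the four shares, since they sum to one).

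Report the stated random-effect model alongside as a check. Baseline-week TST is useful in that check model as a partial safeguard and is redundant with participant fixed effects. Tabulating analysed nights per child and condition would show how much imbalance there is.

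The cost is a few lines of code and of analysis-plan wording, with no new data. Standard errors widen by at most about 1% at the adherence levels in step 3, and by more only if adherence is very low. Children with nights in only one condition contribute nothing to the contrasts.

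This does not deal with night-level selection, where the same evening's circumstances affect both adherence and that night's sleep. That follows from making adherent nights primary and is a separate question.

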## Results

Data collection commenced in February 2022, and the first results are expected to be submitted for publication in 2026.

## Discussion

Ensuring children receive enough good-quality sleep is paramount, given the number worldwide who do not get sufficient sleep for their needs [3]. In fact, it has been argued that addressing sleep health may be a viable way of reducing many health inequities [3]. Therefore, ensuring suitable guidelines exist that are both evidence-based and achievable for families is critical to ensure health impact. At present, we do not have strong evidence that using screens, being physically active, or eating the dinner meal in the hour before bed even impact sleep. In addition, we know that there are many barriers to implementing these behaviors in households. Based on the limited experimental evidence available, we believe that these 3 behaviors might have a limited effect on sleep outcomes in children. It is possible that some, particularly physical activity before bed, might even be beneficial for sleep.

Our proposed trial has several strengths. We have chosen a strong experimental design, are using objective measures of key behaviors to overcome many of the limitations of the current evidence base, and have adequately powered our study to answer our research questions of interest. The HABITS study has been specifically designed to show if these prebedtime behaviors truly influence sleep so that the relevant sleep guidelines can be evidence-based. However, it also has some potential limitations. We will need to ensure that we can recruit a diverse sample, to enable generalizability of findings to a broad demographic. Ideally, we would assess each behavior over the course of a full week, but this was considered inappropriate because of respondent burden. There will be some variation in how families interpret the evening meal and exercise routines suggested, but this should reflect the real world and is appropriate for our pragmatic trial.

## Appendix

Multimedia Appendix 1 Peer-review reports from the Te Kaunihera Rangahau Hauora o Aotearoa / Health Research Council of New Zealand.

## Abbreviations

CONSORT: Consolidated Standards of Reporting Trials
HABITS: helpful activities before it is time for sleep
ICC: intraclass correlation coefficient
PROMIS: Patient-Reported Outcomes Measurement Information System
REDCap: Research Electronic Data Capture
TST: total sleep time
WASO: wake after sleep onset
